##### Outcomes reported by family caregivers

We assess family caregivers’ experiences with the patient undergoing treatment and their individual adaptation using parallel interviews and caregiver-reported outcomes. Identical assessments for family caregivers include the following:◦ Self-report questionnaires for demoralization (DS-II, [37]), depression (PHQ-9, [55]), anxiety (GAD-7, [56]), and suicidal ideation (BSS, [58]), structural deficits (OPD-SFK, [63]), interpersonal difficulties (IIP-32, [62]), emotional dependence (DEQ, [67]), perceived relationship communication (CCS, [73])◦ Diagnostic interview for affective, anxiety, and adjustment disorders (SCID-5, [45]; CIDI, [76])

Complementary assessments for family caregivers include the following: [73].◦ Sociodemographic characteristics (e.g., age, gender, relationship status, children, socioeconomic status, religion/spirituality, degree of kinship/relationship with patient)◦ Semi-structured interviews for prognostic awareness and end-of-life discussions from the family caregiver’s perspective, for their subjective experience with their relative’s illness, as well as the family caregiver’s individual psycho-oncological treatments (frequency, detailed description of treatment) and use of psychosocial support◦ Self-report questionnaires for death anxiety among family caregivers (Death and Dying Distress Scale-Caregivers, DADDS-CG [77]) and a caregiver version of the LOLES [31]. The latter instrument measures the extent to which the caregiver’s life is influenced by inner conflict regarding their relative’s illness. Its 20 items are scored on a 5-point Likert-scale from 0 (not at all) to 4 (completely) with a total score of 80. Higher scores indicate higher distress due to inner conflict.

Specific psychological constructs for family caregivers are assessed using reliable and valid self-report questionnaires: Anticipatory grief (Marwit–Meuser Caregiver Grief Inventory, MM-CGI-SF, [78]), caregiver guilt (Caregiver Guilt Questionnaire, CGQ, [79]), complicated grief after the patient’s death (Inventory of Complicated Grief, ICG, [80]), the patient's quality of dying and death from the caregivers’ perspective (Quality of Dying and Death Questionnaire, QODD, [81]). Detailed descriptions of these questionnaires can be found in a previous publication [59]. We also assess family caregivers' health-related quality of life using the Short-Form Health Survey (SF-8, [82]), an 8-item self-report questionnaire measuring 8 aspects of physical and mental health-related quality of life. Items are scored on a 6-point Likert scale from 0 (not at all) to 5 (very much). Norm-based scores are calculated [83], higher scores are associated with higher health-related quality of life.

##### Therapy process outcomes

We assess therapeutic alliance using the Working Alliance Inventory–Short Revised (WAI-SR), a 12-item self-report questionnaire measuring goal-orientation of the therapeutic working relationship [84, 85]. Items are scored on a 5-point Likert-scale from 1 (rarely) to 5 (always), with a total score ranging from 12 to 60 (Cronbach’s alpha = 0.90) Higher scores indicate a stronger therapeutic alliance with regard to goal-orientation.

We assess psycho-oncological intervention techniques using an adapted version of the Multitheoretical List of Therapeutic Interventions-30 (MULTI-30), a 30-item self-report questionnaire measuring therapeutic interventions in psychotherapy sessions [86]. We adapted the questionnaire for the use in a psycho-oncological setting by adding 9 items that assess typical contents and interventions in this setting [87]. The 39 items are scored on a 5-point Likert-scale from 1 (not at all typical of the session) to 5 (very typical of the session). Higher scores indicate a more frequent use of intervention techniques.

After each therapy session, ORPHYS patients will complete a short questionnaire including the following assessments: anxiety and depression (PHQ-4, [88]), therapeutic alliance (WAI-SR, [84]), and therapeutic agency (Therapeutic Agency Inventory, TAI, [89]). The TAI is a 15-item instrument measuring patients’ perception of their active participation in the therapeutic process. Items are scored on a 5-point Likert-scale from 1 (not true) to 5 (very true), with a total score ranging from 15 to 75 (Cronbach’s alpha = 0.84). Higher scores indicate a stronger sense of actively influencing therapy and bringing about change. Completion of the self-report questionnaire takes approximately 5 to 10 min.

After each session, ORPHYS therapists will document all therapy sessions on a structured, standardized form, which includes the following information:◦ Date, time of the session, and setting◦ Suicidal thoughts and/or intentions based on a standardized operating procedure [90]◦ Short summary of the session◦ Thoughts on transference-countertransference based on the OPD-3 [89]◦ Psychological or psychiatric symptoms (e.g., mood, concentration, level of energy, level of activity), structural deficits based on the OPD-3 [91]◦ Medical treatment◦ Occurrence and severity of adverse events (AE, new psychological or physical symptoms, progress of disease, hospital admission, death, suicidal thoughts or attempts, difficulties in relationships or other areas of life) rated on a scale from 1 (mild) to 3 (severe), likelihood of an AE being related to the therapy rated on a scale from 1 (none) to 5 (definitely) [92]◦ Dropout (treatment, study, treatment-and-study dropout, or dropout due to adverse event)

Further, ORPHYS therapists will complete the WAI-SR [84].

Trained observers rate audio recordings and transcripts of therapy sessions to assess insight into repetitive dysfunctional relationship patterns and defense mechanisms. Insight is rated on a 5-point Likert-scale from 0 (not at all) to 4 (very much) using the 12-item Insight into Conflictual Relationship Patterns Scale (ICR, [93]). The total score ranges from 0 to 48. Higher scores indicate a more complex understanding of internal states and interpersonal processes. Defense mechanisms are rated by ranking the 150 items of the Q-sort version of the Defense Mechanisms Rating Scale (DMRS-Q, [94]) on an ordinal scale from 1 to 7. Qualitative and quantitative scores will be calculated using the DMRS-Q web-app (https://webapp.dmrs-q.com/).

Dosage and content of TAU treatment will be documented by the study personnel on a standardized form, which includes the following information.◦ Date, time of the session, and setting◦ Short summary of the session◦ Occurrence and severity of adverse events◦ Dropout

A semi-standardized section of the diagnostic interview will assess treatment dosage and frequency as well as utilization of further psychosocial support services (e.g., relaxation training, self-management programs).

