### Recruitment {20}

We will recruit participants at the study centers in Hamburg, Düsseldorf, and Würzburg. They are either patients who seek psychosocial support through the study centers’ psycho-oncology clinics or patients who are referred to the study. Under the supervision of a licensed psychotherapist or senior physician, experienced trained study personnel will initially screen patients for inclusion criteria via in-person assessment. Trained study personnel with at least advanced psychotherapeutic training will conduct a comprehensive recruitment interview and hand out written standardized patient information on both treatment arms. After obtaining written informed consent, included patients will complete the baseline assessment including self-report measures and a diagnostic interview. Subsequently, included patients will be randomized.

Study personnel will contact patients’ family caregivers via telephone for participation upon patients’ consent. Study personnel will give comprehensive study information and if family caregivers verbally consent to participate, they will be sent written informed consent and study information via mail. In the event of a patient’s death, participating family caregivers will receive another questionnaire 3 months after the patient’s death (post-death survey). Follow-up for deceased patients will be performed until 1 year after inclusion of the last participant.

Diagnostic interviews will be conducted via telephone or face-to-face by trained advanced psychology or medical students; self-report questionnaires and follow-up assessments will be sent via mail. We will document the number of excluded participants as well as reasons for exclusion. For non-responder analyses, we will collect basic demographic and medical data from non-participants upon their consent.

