## Assignment of interventions: blinding

### Who will be blinded {24a}

Since this is a psychotherapy study with two active intervention groups, blinding of participants and therapists is not possible. Recruitment interviews and assessments (diagnostic interviews, mailing of self-report questionnaires) are conducted only by trained, clinically experienced research assistants, who have no knowledge of patients’ treatment allocation.

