### How will blinding be achieved {24b}

Before each assessment, participants are reminded to not disclose their treatment allocation to study personnel. Study personnel not involved in data collection will perform statistical analysis. Statistical support is provided by the Department of Medical Biometry and Epidemiology at the University Medical Center Hamburg-Eppendorf (SL).

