### Procedure for unblinding if needed {24c}

N/a, trial is non-blinded.

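### The diagnostic interview meant to be blinded also asks about treatment dosage and frequency, which will usually reveal the arm, and no safeguard for the mental-disorder rating is stated

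*Protocol article*

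**What the plan says.** Section 24a accepts that patients and therapists cannot be blinded but keeps the assessors blinded: the diagnostic interviews, among other assessments, fall to staff "who have no knowledge of patients’ treatment allocation". Section 24b adds a safeguard: "Before each assessment, participants are reminded to not disclose their treatment allocation to study personnel".

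The end of Therapy process outcomes places a treatment-use section inside the interview those assessors conduct: "A semi-standardized section of the diagnostic interview will assess treatment dosage and frequency as well as utilization of further psychosocial support services".

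The interview is also the source of an efficacy outcome. Under Secondary outcomes, affective and anxiety disorders are diagnosed with the SCID for DSM-5 and adjustment disorder with a CIDI module. Trial design (section 12) schedules diagnostic interviews at baseline, 6 and 12 months. Section 24c, on unblinding procedures, reads: "N/a, trial is non-blinded".

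**The concern.** Patients are told to keep their arm to themselves and are then asked, in the same interview, how much treatment they had and how often. The two arms are defined by very different schedules, so an honest answer comes close to naming the arm.

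Mental-disorder diagnosis is the first secondary outcome the protocol lists, and the only primary or secondary outcome that an interviewer rates. Patients and therapists know the arm, so assessor blinding is the main protection of this rating against expectation. If an interviewer learns the arm before settling a diagnosis, judgement on borderline symptoms can lean towards the expected result, and a later report could not properly describe the diagnoses as blinded.

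**Working it through.** **Inputs, all from the protocol**
- ORPHYS: weekly sessions, 15 to 31 in total (Treatment dosage).
- TAU: no minimum number, often one session every 3 to 4 weeks over a year (TAU, control group).
- Expected ORPHYS course: 24 sessions with 30% of sessions cancelled, lasting about 8 months (section 25a).
- Interviews after randomization: 6 and 12 months after baseline (section 12).

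**Reproducing the protocol's own figure**

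Weeks needed = sessions / (1 − 0.30). 24 / 0.70 = 34.3 weeks, and 34.3 / 4.348 weeks per month = 7.9 months. This matches the stated 8 months, so a weekly schedule with 30% cancelled is the right reading.

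**Expected sessions by the 6-month interview (26.1 weeks)**
- ORPHYS: 26.1 × 0.70 = 18.3, about 18.
- TAU: 26.1 / 4 = 6.5 to 26.1 / 3 = 8.7.

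These counts assume that treatment starts at baseline. Randomization and first contact by the therapist come later. With an assumed delay of 4 weeks in both arms, 22.1 weeks remain: ORPHYS 22.1 × 0.70 = 15.5, TAU 22.1 / 4 = 5.5 to 22.1 / 3 = 7.4. The gap stays wide. With an expected course of about 8 months, many ORPHYS patients will also still be in weekly therapy at 6 months, so frequency alone is informative.

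**How well the count separates the arms (illustration)**

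Assume ORPHYS sessions are binomial (26 weeks, attendance 0.7) and TAU sessions are Poisson with mean 6.5 or 8.7. The best single cut-off, averaged over the two arms, then classifies:
- TAU mean 6.5, cut at 13 sessions: 98.7% correct.
- TAU mean 8.7, cut at 14 sessions: 95.7% correct.

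The protocol gives neither distribution. Early stopping in ORPHYS and varying TAU frequency would lower these percentages.

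**At 12 months (52.2 weeks)**

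TAU: 52.2 / 4 = 13.0 to 52.2 / 3 = 17.4, against 15 to 31 for a completed ORPHYS course. Counts overlap more, but weekly against 3- to 4-weekly sessions still points to the arm.

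**What the protocol leaves open**

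| Situation | 6-month diagnosis | 12-month diagnosis |
|---|---|---|
| Section asked before the rating | exposed | exposed |
| Section asked after the rating, same interviewer returns | protected | exposed |
| Section asked after the rating, new interviewer | protected | protected |

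The protocol does not say which row applies, or whether someone else asks the section.

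**The case against.** Several counter-arguments have force.

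**The order of the interview is not stated.** A journal article need not give it, and if the treatment section follows the diagnostic rating, the 6-month diagnosis is safe. A reader might infer that the plan abolishes assessor blinding, or that an interviewer necessarily carries knowledge of the arm to 12 months. The text supports neither, because both depend on order and on who returns. What stands is that the stated procedures pull against each other: the interviewer who must not know the arm is given the question that discloses it.

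**TAU is flexible.** It may vary between and within sites and has no minimum, and some ORPHYS patients will start late or stop early. The answer is therefore a strong clue and not proof in every patient.

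**The outcome is of limited rank.** Section 27a treats everything except the primary analysis as exploratory, with descriptive p-values. The primary outcome, the DS-II, is a self-report questionnaire. A reader might infer that the confirmatory result is compromised, but the interviewer does not rate it. Structured instruments also narrow a rater's discretion, so blinding is not the only protection. This limits the consequence without removing the conflict.

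**The wording differences are minor.** Section 24c answers an item on unblinding procedures, and its phrase is loose shorthand in a trial with open patients and therapists. Section 20 says that diagnostic interviews are done "by trained advanced psychology or medical students", whereas 24a speaks of research assistants with clinical experience. Students can be employed as research assistants, so this is no firm contradiction.

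**Conclusion.** The point holds in a bounded form. Sections 24a and 24b promise blinded diagnostic interviews, and Therapy process outcomes puts into those interviews questions whose answers will usually identify the arm: about 18 against 6.5 to 8.7 expected sessions by 6 months, with some overlap. No safeguard for the rating is stated.

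It concerns the 6- and 12-month interviews in both arms and not the baseline interview, which precedes randomization. It touches one interviewer-rated secondary outcome, analysed as exploratory, and leaves the self-reported primary outcome alone. The documents do not show that any diagnosis will be biased, nor in which direction or by how much.

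The session counts rest on the protocol's weekly schedule, its 30% cancellation rate and its description of usual TAU frequency. The classification percentages rest on assumed distributions and are only illustrative. The change should be made, because the exposure is avoidable at little cost.

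**What to change.** Either of two changes protects the rating.

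1. **Take the section out of the interview.** Section 25b already has each ORPHYS and TAU session documented on a standardized form, so dosage and frequency can come from there. Move use of other psychosocial support, and dosage of TAU given by external providers, to the mailed questionnaire. Someone other than the diagnostic rater should enter these items and complete the TAU form, because section 26 gives data entry to research assistants.
2. **Keep it in the interview, but last.** Ask it only after the diagnostic ratings are locked, and use a different interviewer at 12 months.

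In both cases, record any occasion on which an assessor learns the arm. Align section 24c with 24a by stating that patients and therapists are unblinded and diagnostic assessors are blinded. Using one description of the interviewers in sections 20 and 24a would tidy the text.

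The cost is small. The first option may give slightly less complete dosage data, mainly for TAU patients referred elsewhere, and adds a few items to a questionnaire that already takes 30 to 40 minutes. Both options need some planning of who interviews or who enters data. Recruitment runs to December 2027, so most follow-up interviews can still be covered.

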##### Treatment adherence

To investigate treatment adherence, ORPHYS sessions will be audio-recorded, transcribed, and rated using the Penn Adherence/Competence Scale for Supportive-Expressive Dynamic Psychotherapy [42]. Treatment adherence will further be ensured by providing and documenting the regular supervision sessions.

### Harms {17}

After each ORPHYS and TAU session, occurrence and severity of adverse events (new psychological or physical symptoms, progress of disease, hospital admission, death, suicidal thoughts or attempts, difficulties in relationships or other areas of life); serious adverse events (death, life-threatening event, prolonged or persistent disability or incapacity); and unanticipated events as well as their likelihood of being related to the treatment will be documented on a structured, standardized form [62, 92]. All adverse, serious adverse, and unanticipated events will be reported in trial publications.

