### Trial design {12}

We will conduct a two-arm, parallel, pragmatic randomized controlled trial with an active control group and 5 points of assessment (pre-intervention [baseline], 3, 6, 9, and 12 months after baseline). Patients in the intervention group will receive a manualized short-term psychodynamic psychotherapy (ORPHYS), while patients in the control group will receive usual psycho-oncological treatment (TAU). Primary and secondary outcome measures will be assessed using diagnostic interviews (baseline, 6 months and 12 months after baseline) as well as self-report questionnaires, and electronic medical patient records (baseline, 3, 6, 9, and 12 months after baseline). Block randomization with an allocation ratio of 1:1 is carried out using electronically generated numbers.

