#### Treatment dosage

In ORPHYS, patients receive 15 to 31 weekly therapy sessions lasting 50 min. This number of therapy sessions is in line with the German Psychotherapy Standard for short-term psychotherapy and typical short-term psychotherapies [41]. It includes 3 to 7 diagnostic sessions, and additional 12 to 24 psychotherapy sessions, depending on patients’ individual needs and goals. The number of sessions translates into approximately 5 to 11 months of treatment duration, taking into account expectable interruptions due to physical condition, medical procedures, or rehabilitation measures. Sessions may be provided via video or telephone. ORPHYS treatment is considered complete per-protocol (PP), if patients have received at least 15 sessions.

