#### TAU (control group)

In line with our pragmatic study approach, content and frequency of TAU sessions may vary between and within the study sites. Details of TAU treatment will be documented by the study personnel on a standardized form (see section Therapy process outcomes). Patients receive routine psycho-oncological treatment as provided by the study centers. TAU includes supportive psycho-oncological interventions according to the German Psycho-Oncology Guideline. There is no requirement for a minimum number of treatment sessions. The dosage is flexibly adapted to individual cases and often includes one session every 3 to 4 weeks over the course of a year.

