##### Other variables

We assess adverse events using the Inventory for Assessing Negative Effects of Psychotherapy (INEP), a 21-item self-report questionnaire measuring to what extent patients experience intrapersonal and interpersonal changes as well as changes regarding work, stigmatization, and therapeutic misconduct [62]. Patients are also asked to indicate whether they attribute these changes to the therapy itself. Six items are scored on a 7-point scale from − 3 (worsening) to 3 (improvement); fifteen items are scored on a 4-point Likert-scale from 0 (not at all) to 4 (completely). If patients attributed changes to the therapy itself, frequencies, means, and standard deviations of negative (− 3 to 1), no (0), and positive changes (1 to 3) are calculated ((Cronbach’s alpha = 0.86).

We assess structural deficits using the OPD-Structure Questionnaire (OPD-SFK, [63]), a 12-item self-report questionnaire measuring personality functioning based on the Operationalized Psychodynamic Diagnosis (OPD, [64]). Items reflect the subscales self-perception, shaping contact, and key relationship models. They are scored on a 5-point Likert-scale from 0 (not at all) to 4 (completely), with a total score ranging from 0 to 48 (Cronbach’s alpha = 0.89). Higher scores indicate higher impaired personality functioning.

We assess interpersonal difficulties using the Inventory of Interpersonal Problems (IIP-32), a 32-item self-report questionnaire measuring distress due to interpersonal problems on eight subscales [65, 66]. Items are scored on a 5-point Likert-scale from 0 (not) to 4 (very much), with a total score ranging from 0 to 128 and subscale scores each ranging from 0 to 32 (Cronbach’s alpha = 0.86) [66]. Higher total scores indicate higher distress due to interpersonal problems; higher subscale scores indicate specific dysfunctional relational patterns.

We assess emotional dependence on others using an 18-item version [67] of the Depressive Experiences Questionnaire (DEQ), a self-report questionnaire measuring feelings of helplessness, loneliness, and fear of rejection due to disruption in a relationship [68–70]. Items are scored on a 7-point Likert-scale from 1 (strongly disagree) to 7 (strongly agree), with a total score ranging from 18 to 126. Higher scores indicate higher dependence on others to regulate emotional distress (Cronbach’s alpha = 0.74–0.83) [71].

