## Data collection and management

### Plans for assessment and collection of outcomes {25a}

Figure 1 shows the data collection process. After enrollment in the study, participants complete the baseline assessment (diagnostic interview, self-report questionnaire) within 14 days and are randomized afterwards. Post-randomization assessments are collected at fixed intervals (3, 6, 9, and 12 months after baseline assessment). The primary outcome demoralization is measured at baseline, 3, 6, 9, and 12 months after baseline. Based on an expected treatment duration of 24 sessions and a 30% session cancellation rate, we expect treatment to last about 8 months. Taking into account the range of treatment duration from 15 to 31 sessions, we expect completion of treatment after 5 to 11 months. Medical information including end-of-life care will be collected via medical chart review (electronic patient file, medical reports). We will conduct two semi-structured interviews with participating family caregivers at 6 and 12 months. Table S1 shows the planned assessments and corresponding time points.

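### Adverse events are logged per session, so session-form counts come from unequal observation in the two arms and are not comparable between them

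*Protocol article*

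**What the plan says.** **Trigger.** Under Harms {17}, "After each ORPHYS and TAU session, occurrence and severity of adverse events", together with serious and unanticipated events and their likely relation to treatment, go onto a structured form. All of them are to be reported in trial publications.

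**Contact frequency.** Under Treatment dosage, "In ORPHYS, patients receive 15 to 31 weekly therapy sessions lasting 50 min". Under Plans for assessment and collection of outcomes {25a}, "Based on an expected treatment duration of 24 sessions and a 30% session cancellation rate, we expect treatment to last about 8 months", and across the session range "we expect completion of treatment after 5 to 11 months". Under TAU (control group), the dose is flexible and "often includes one session every 3 to 4 weeks over the course of a year". That section sets no minimum number of sessions, whereas the abstract says TAU includes at least one. TAU may also be given by external providers (eligibility criteria for sites {14b}).

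**Recorders and forms.** Under Therapy process outcomes, ORPHYS therapists document suicidal thoughts under a standard procedure, event severity from 1 to 3 and relatedness from 1 to 5. The TAU form is completed by study personnel. Its listed contents cover occurrence and severity of adverse events, with no relatedness rating and no separate suicidality item.

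**Other sources.** Under Trial design {12}, both arms are assessed by diagnostic interviews "as well as self-report questionnaires, and electronic medical patient records (baseline, 3, 6, 9, and 12 months after baseline"). The INEP is the self-report measure of negative effects. Under Other variables, for changes attributed to therapy, frequencies, means and standard deviations of "negative (− 3 to 1), no (0), and positive changes (1 to 3) are calculated".

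**The concern.** If recording happens only at sessions, the arm with more sessions has more chances to record an event, even when true event rates are equal. Here session frequency is a component of the intervention, so the difference in observation is built in and does not average out with sample size. It also changes over time: ORPHYS is observed more closely early on, and its session forms stop when therapy ends.

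The difference in recorders and forms adds to this. Under the data monitoring section {28a}, an event becomes an adverse treatment reaction when it is treatment-related. If relatedness is rated routinely in one arm only, that classification is not on an equal footing, although the Harms section promises relatedness in both arms.

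The stake is how the harms results will be read. Readers of a two-arm trial will set the published events side by side. Session-form counts could make ORPHYS look more harmful during therapy, or leave minor harms under TAU unrecorded. An analysis plan can attach a caveat or a denominator, but it cannot recover events that were never collected.

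**Working it through.** **Inputs.** ORPHYS: 15 to 31 weekly sessions, 24 expected, 30% cancelled, about 8 months (range 5 to 11). TAU: one session every 3 to 4 weeks over a year. Assumptions: a 52-week year, TAU at its stated typical frequency, and no TAU cancellations, since the protocol gives no TAU cancellation rate.

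**1. Reproduce the protocol's duration.** Weeks = sessions / (1 − 0.30).
- 24 / 0.7 = 34.3 weeks = 7.9 months, which matches the stated 8.
- 15 / 0.7 = 21.4 weeks = 4.9 months, which matches the stated 5.
- 31 / 0.7 = 44.3 weeks = 10.2 months, a little under the stated 11.

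**2. Ratio of recording occasions while ORPHYS runs.** ORPHYS has 0.7 sessions per week, TAU 1/4 to 1/3.
- 0.7 / (1/3) = 2.1 and 0.7 / (1/4) = 2.8.
- Taking 31 sessions over the stated 11 months (47.7 weeks) gives 0.65 per week and a ratio of 2.0 to 2.6.

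**3. Ratio over 12 months.** TAU has 52/4 = 13 to 52/3 = 17.3 sessions.

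| ORPHYS sessions | Ratio to 17.3 | Ratio to 13 |
|---|---|---|
| 15 | 0.9 | 1.2 |
| 24 (expected) | 1.4 | 1.8 |
| 31 | 1.8 | 2.4 |

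**4. Reversal after ORPHYS ends.** If ORPHYS ends at 8 months, 4 months (17.3 weeks) remain. A TAU patient who continues has 17.3/4 = 4.3 to 17.3/3 = 5.8 further occasions; an ORPHYS patient has none.

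**5. Sensitivity to TAU cancellations.** If 30% of TAU sessions are also cancelled, the in-treatment ratio is 3 to 4. The 12-month ratio at 24 sessions is 24/(0.7 × 17.3) = 2.0 to 24/(0.7 × 13) = 2.6.

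**6. Which events are affected.** The protocol states no recall window. Purely as an illustration, suppose an event is noted only if still present at a session and sessions are evenly spaced. The chance of capture is then min(1, event duration / session interval), with intervals of 1/0.7 = 1.4 weeks in ORPHYS and 3 to 4 weeks in TAU.

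| Event lasts | ORPHYS | TAU |
|---|---|---|
| 1 week | 0.70 | 0.25 to 0.33 |
| 2 weeks | 1 | 0.50 to 0.67 |
| 3 weeks | 1 | 0.75 to 1 |
| 4 weeks | 1 | 1 |

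The gap is large for short events and disappears for lasting ones. If patients are asked about the whole interval since the previous session, it is smaller throughout.

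**7. INEP bands.** As printed, the negative band includes 0 and 1. A score of 0 is therefore both negative and unchanged, and a score of 1 both negative and positive. Separately, the fifteen remaining items are called 4-point but run from 0 to 4, which is five values.

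**The case against.** The strongest reply is that the article states no between-arm test or rate comparison of harms. It promises only to report all events, and tabulation with exposure may well be in the analysis plan, which is not shown. This stands, and it limits the point to raw session-form counts. It does not remove the point, because the collection schedule is fixed here.

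A reader might infer three stronger things that the document does not support:

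- **That TAU patients without sessions go unobserved.** They have no session form, but self-report questionnaires (including the INEP and the suicidal ideation scale) apply to both arms. Diagnostic interviews, chart review and dropout reasons remain as well. These sources are not a full substitute. INEP results are calculated for changes attributed to therapy, its time points are in a supplementary table not shown, and the hospital-use items listed for chart review concern the last 30 days of life. Whether zero-session TAU patients can exist at all depends on reconciling the abstract with the TAU section.
- **That ORPHYS is observed two to three times as often throughout the trial.** This holds only while ORPHYS runs. At 15 sessions the 12-month totals are about equal.
- **That deaths, progression and admissions will be overcounted in ORPHYS.** Death is recorded outside the session forms, progression within the last 3 months is a planned covariate, and an admission can still be reported at the next session. The effect falls mainly on transient or mild events.

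It can also be said that the INEP band is a separate slip, probably a lost minus sign. That is fair; it is a minor correction and carries no weight in the main argument.

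**Conclusion.** The point holds in limited form. Session-form capture of adverse events is unequal by arm: about 2.1 to 2.8 times as many occasions in ORPHYS during its treatment period, and about 1.4 to 1.8 times over 12 months at 24 sessions (0.9 to 2.4 across 15 to 31). The direction reverses after ORPHYS ends if TAU continues. The figures rest on the stated typical TAU frequency without TAU cancellations; allowing for those raises them.

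The listed form contents also disagree with the Harms section on relatedness in TAU. Together these make raw session-form counts, chiefly of short or mild events, unsuitable for comparison between arms. They do not show that all the harms data are biased or uninterpretable. This should be changed while recruitment is open; it does not touch the primary analysis.

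**What to change.** 1. Collect the adverse event categories of the Harms section with identical items at the existing 3-, 6-, 9- and 12-month assessments in both arms. The self-report questionnaire is the natural place, since it does not require interviewers to discuss therapy.
2. Use chart review for death, hospital admission and progression over the whole follow-up in both arms.
3. Base any between-arm presentation of harms on these two sources.
4. Keep session forms for real-time safety monitoring. Report them with the number of sessions per arm and a statement that the counts are not comparable.
5. Align the TAU form with the Harms section so that relatedness is recorded in both arms, and reconcile the abstract and the TAU section on the minimum number of sessions.
6. Correct the INEP bands so that they do not overlap, and correct the description of the 0-to-4 items.

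**Cost.** A few extra questionnaire items, a revised TAU form and an amendment during recruitment, which runs to December 2027. Patients enrolled since October 2025 may lack the new items at early time points. A three-month recall will miss some minor events, but on the same schedule in both arms.
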